#### Mediation analysis

To evaluate plausible mechanisms of change in treatment [126], both causal mediation analysis [127, 128] and structural equation modeling (SEM) [129, 130] will be conducted. Causal mediation analysis will be performed using the *mediation* package [131] to compute average causal mediation effects (ACME) and average direct effects (ADE), facilitating inferences about temporally sequenced mediators such as ER and social cognition factors. Simultaneously, SEM will be harnessed using the *lavaan* package to assess multiple mediators while accounting for the nested, longitudinal data structure and measurement error [129]. Latent variable analysis, including core psychological concepts (e.g., anhedonia, personality) using confirmatory factor analysis (CFA) with FIML estimation and other missing data management strategies described above, will be conducted. These complementary methods provide both causal inferences under plausible outcome frameworks and parameter estimates of indirect effects, enabling a stringent and theory-driven understanding of how the Digital PAI operates.

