The remaining aims were exploratory. We aim to examine theory-driven *mediators* (variables that account for why and how the app works) [52] and *moderators* (or effect modifiers; variables that pinpoint for whom the app works) [53]. Diverse theory-driven neurocognitive and psychosocial variables are collected, as detailed in the next section, while maintaining an exploratory approach due to the limited existing studies on this topic.

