## Method

### Study design

Details about this trial are captured in the SPIRIT (Standard Protocol Items: Recommendations for Interventional Trials) checklist [54, 55] in Appendix A of the online supplemental materials (OSM) and Fig. 1. This study is a two-arm, parallel-group RCT that aims to test the efficacy of Digital PAI relative to a Self-Monitoring Placebo control in adults with mild-to-moderately severe anxiety or depression. After providing informed consent and completing the Qualtrics-administered baseline self-report battery, participants will be randomized in a 1:1 ratio (*n* = 600 per condition) using a computer-generated random number sequence embedded in the Qualtrics platform. In other words, participants are randomized into the Digital PAI or Self-Monitoring Placebo control group at the end of the baseline assessment using the built-in randomizer function in Qualtrics. The sequence is stratified by race and sex to ensure balanced allocation across key demographic strata. Immediately after completing the baseline assessment, Qualtrics automatically assigns participants to either the 6-week, low-intensity, guidance-on-demand Digital PAI or the 6-week Self-Monitoring Placebo, both of which are accessed via the mEMA Ilumivu software. The allocation sequence is concealed from the lead principal investigator (PI) and study analyst via automated assignment coding; both remain blinded to treatment group assignments until after data collection is complete.

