
**Table 2 Tab2:** Summary of digital positive affect intervention (PAI) content

Week	Session	Session Title	Key Content and Intervention Strategies
Week 1	Session 1	Is it difficult for you to feel positive emotions?	Psychoeducation on anhedonia, the positive affect system (wanting, liking, learning), and the consequences of low positive affect; introduces case examples to contextualize symptom profiles.
	Session 2	How will this online intervention work for you?	Orientation to intervention structure, intervention fit and readiness assessments, rationale for targeting positive affect, and overview of modules.
	Session 3	Let’s get started	Guidance on using practice sheets, daily skill rehearsal, self-monitoring, and intervention pacing; introduces symptom tracking and exercise compliance strategies.
Week 2	Session 4	The triad of feelings, thoughts, and actions	Introduces the mood cycle model; teaches the interplay between cognitions, behaviors, and physical sensations in shaping mood; begins emotion labeling and upward spiral training.
Week 3	Session 5	Actions toward feeling better	Behavioral activation module focusing on identifying, scheduling, and practicing rewarding activities; includes activity monitoring, mastery-building, savoring, and troubleshooting motivational barriers.
Week 4	Session 6	Attending to the positive	Cognitive strategies to enhance attentional focus on positive experiences: finding silver linings, taking ownership of successes, and imagining positive outcomes to strengthen reward anticipation.
Week 5	Session 7	Building positivity	Positive affect cultivation through loving-kindness, gratitude, generosity, and appreciative joy exercises; emphasizes relational and compassion-based positive emotion generation.
Week 6	Session 8	Contributing to the journey after the intervention	Consolidation of gains, maintenance planning, relapse prevention, progress assessment, and preparation for long-term self-guided practice.

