Simultaneously, this RCT includes diverse methodological aspects to enhance ecological validity (generalizability) and internal validity. First, the utilization of piecewise MLM provides a fine-grained assessment of change outcomes [149], facilitating the separation of proximal and distal outcomes. Second, leveraging causal mediation analysis and SEM enables inquiries into whether enhancements in the positive valence system constructs (e.g., anhedonia, attentional control, reward sensitivity) function as plausible explanatory treatment mechanisms [150, 151], thereby identifying treatment targets consistent with the Research Domain Criteria (RDoC) framework [152]. Third, meta-learning algorithms (e.g., T-learner) will be implemented to develop prescriptive prediction models [137] that inform which subgroup benefits most from Digital PAI compared to the Self-Monitoring Placebo. Such efforts improve accuracy and clinical interpretability when examining treatment effect heterogeneity, moving beyond answering questions about between-group treatment efficacy. Finally, for randomly selected individuals, data extracted from passive sensor wearables can aid in identifying context- and time-specific variables that function as engagement metadata and moderators, potentially informing just-in-time adaptive interventions [153].

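### The exploratory mediation analysis is described as giving causal inferences, but only the arm is randomised, so the indirect effects are causal only under an assumption the protocol article does not state

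*Protocol article*

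**What the plan says.** The Mediation analysis section plans two methods. The first is causal mediation with the *mediation* package, "to compute average causal mediation effects (ACME) and average direct effects (ADE), facilitating inferences about temporally sequenced mediators". The second is structural equation modelling, "using the *lavaan* package to assess multiple mediators while accounting for the nested, longitudinal data structure and measurement error". The section concludes: "These complementary methods provide both causal inferences under plausible outcome frameworks and parameter estimates of indirect effects".

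The Discussion says these methods will show whether "enhancements in the positive valence system constructs (e.g., anhedonia, attentional control, reward sensitivity) function as plausible explanatory treatment mechanisms", and links this to finding treatment targets. Its paragraph on strengths presents the mediation methods as a rigorous test of how change comes about.

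Two other statements set the context. In Study design, "participants will be randomized in a 1:1 ratio"; nothing else is randomised apart from who receives a wearable. In Study aims and hypotheses, mediation falls under "The remaining aims were exploratory".

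**The concern.** Randomising the arm protects two comparisons: arm on mediator and arm on outcome. It does not protect the association between mediator and outcome within an arm, and the ACME is built on that association. A person who is generally more distressed, or who reports more negatively, will score worse on both a process scale and the GAD-7 or PHQ-9, whether or not one causes the other.

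The design makes such shared causes likely. Table 1 shows most candidate mediators (for example ERQ, PVSS, DARS, ACS) given as self-reports at the same visits as the GAD-7 and PHQ-9. The intervention is also meant to move several of these processes together, so one process can stand in for another.

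Both planned methods rest on the same condition, so agreement between them does not test it. The sensitivity analyses named elsewhere in the Statistical analysis plan section concern missing data and the model for binary outcomes. At stake is the answer to how the intervention works: a process that merely changes alongside symptoms could be reported as a causal mechanism and a treatment target.

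**Working it through.** The article gives no figure for the mediation analysis, so there is none to reproduce. The check asks how often a single-mediator ACME appears when the truth is zero.

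**Inputs**
- Completers: 1,200 × (1 − 0.50) = 600, or 300 per arm (Sample size and power).
- Arm effect on the mediator, *a*: 0.1, 0.2 and 0.3 SD. Assumed. The article expects between-arm effects of d = 0.2 to 0.5; 0.1 is added as a weak case.
- Mediator-outcome correlation from a stable shared cause, ρ: 0.3 to 0.5. Assumed; the article gives none.
- Two-sided 5% level. Assumed; sidedness is not stated.

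**Set-up.** Mediator and outcome both have unit variance within arm, share the stable cause, and are each shifted by the arm through separate routes. The mediator has no effect on the outcome, so the true ACME is 0. In the linear case the estimate is *a* × *b*, where *b* is the mediator coefficient in the outcome model that also contains the arm.

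**Step 1: bias.** Here *b* converges to ρ instead of 0, so the ACME converges to *a*ρ. If the arm effect on the outcome is *c*, the falsely mediated share is *a*ρ/*c*. With *c* = *a* this equals ρ: 30% to 50%.

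**Step 2: how often it is significant.** With ρ = 0.3 the test of *b* has z ≈ 0.3/√(0.91/597) = 7.7, so *b* is practically always detected. The rate is then close to the power for the arm effect on the mediator, Φ(*a*√(300/2) − 1.96).

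| *a* (SD) | *a*√150 | Closed form | Simulation, ρ 0.3 to 0.5 |
|---|---|---|---|
| 0.1 | 1.22 | 23% | 21–23% |
| 0.2 | 2.45 | 69% | 66–67% |
| 0.3 | 3.67 | 96% | 96–98% |

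The simulation used 1,000 trials per cell and a Monte Carlo 95% interval for *ab*. With ρ = 0 the interval excluded zero in at most about 5% of trials, so the method is sound when its assumption holds. With ρ = 0.1 the rates were 14%, 45% and 65%. With all 1,200 analysed and ρ of at least 0.2 they were 37–39%, 93–94% and about 100%.

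**Step 3: adjusting for baseline mediator and baseline outcome.** If the shared cause is stable, all four measurements correlate at ρ, and the coefficient becomes ρ/(1 + 2ρ): 0.3/1.6 = 0.19 and 0.5/2.0 = 0.25. The false share falls to about 18–25% (simulation and closed form agree). The false-positive rate does not fall. Adjustment cuts the mediator's residual variance to 1 − 2ρ²/(1 + ρ), which is 0.86 and 0.67, and so sharpens the arm effect on the mediator. At *a* = 0.2 the closed form gives Φ(0.2√150/√0.8615 − 1.96) = Φ(0.68) = 75% and Φ(0.2√150/√0.6667 − 1.96) = Φ(1.04) = 85%.

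**Step 4: joint mediators.** One mediator truly acts (*b* = 0.4, shifted 0.3 SD). A bystander correlates with it at 0.3 to 0.5 and is shifted 0.1 to 0.5 SD. With 600 analysed, the bystander is flagged in 16% to 100% of trials when analysed alone and in 0.3% to 5.6% when the true mediator is in the same model. This gain needs the true mediator to be measured; a joint model does not deal with unmeasured causes.

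**The case against.** The strongest reply is that this is an exploratory aim. The article labels it so, speaks of plausible mechanisms, qualifies the causal phrase by reference to outcome frameworks, and gives no rule for declaring a mechanism. It already plans a multiple-mediator model. Covariates and sensitivity analyses for mediation may sit in a fuller plan that is not shown.

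Much of this stands. Missing technical detail is not the fault, and the exploratory label limits the harm. What remains is the published statement that the methods provide causal inferences, with no condition attached to the mediator-outcome path. The Discussion does not repeat the exploratory label when it speaks of rigorous tests and treatment targets. Nor does the article say that mechanism statements will rest on the joint model rather than on single ACMEs.

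A reader might go further and infer three things that the documents do not support.

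- *That almost any process the intervention shifts would be declared a mechanism.* No declaration rule exists, and at a 0.1 SD shift the false rate is about one fifth. It reaches 91–100% only among trials in which the shift and the mediator-outcome association are both detected. That ACMEs will be run one mediator at a time is also inferred from where the article places multiple mediators; it is not stated.
- *That Week 3 is the only mediator measurement before the Week 6 outcome, ahead of content such as* "Positive affect cultivation through loving-kindness, gratitude, generosity, and appreciative joy exercises". This holds for the scales in Table 1. But affect is also rated three times daily through all six weeks, and the sections on brief EMAs and proximal outcomes name those ratings as possible mediators. Week 3 also already contains savoring and rewarding activities.
- *That Week 6 mediators with Month 3 outcomes, adjusted for the Week 6 outcome, should be the main sequence.* That adjustment blocks the route by which a during-treatment mechanism acts. With an assumed shift of 0.3 SD, *b* = 0.4 and symptom carry-over of 0.7, the true indirect effect is 0.3 × 0.4 × 0.7 = 0.084. Simulation recovered 0.085 without the adjustment and 0.000 with it.

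**Conclusion.** The point holds as one of wording and interpretation, with a quantifiable risk behind it. Under the assumptions in the working, a single-mediator ACME would be significant in about two thirds of trials at a 0.2 SD shift and about 96% at 0.3 SD although the true value is zero, with about 30–50% of the arm effect falsely mediated. The rates depend mainly on the size of the shift. The false share depends on the assumed correlation and on equal arm effects on mediator and outcome. Neither can be checked from the article.

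The primary efficacy comparison is unaffected. Because the aim is exploratory, this is a recommended improvement and not a threat to the trial's main conclusion.

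**What to change.** Amend the Mediation analysis section as follows.

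1. Replace the claim of causal inferences with indirect effects under the assumption of no unmeasured mediator-outcome confounding, labelled exploratory. Bring the Discussion into line.
2. Report with each ACME a sensitivity analysis giving the residual mediator-outcome correlation at which it becomes zero.
3. Base mechanism statements on the multiple-mediator model already planned, not on single-mediator ACMEs.
4. Adjust every mediator and outcome model for the baseline mediator and the baseline outcome (for GAD-7 and PHQ-9, Table 1 places the pre-treatment score at screening). State that this reduces the bias without removing it or lowering the false-positive rate, so it does not replace item 2.

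The cost is a few sentences and some extra model runs on data already being collected. The downside is smaller indirect effects and more cautious claims about mechanism.

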#### Moderation analyses

Moderation analyses will be conducted to answer the question, ‘Who benefits most from Digital PAI (treatment) compared to Self-Monitoring Placebo (control)?’ We will implement precision medicine approaches for moderation analyses. The T-learner, S-learner, doubly robust (DR), and X-learner estimation approaches (also referred to as meta-learning algorithms) will be utilized to estimate participant-level between-group effects by training independent models for the Digital PAI and Self-Monitoring Placebo groups [132]. This method facilitates the estimation of conditional average treatment effects (CATEs) [133]. Simultaneously, the Group Average Treatment Effects (GATES) method will divide participants into data-driven strata based on the expected benefit of treatment relative to control and compare average treatment effects across these strata [134, 135]. These approaches enable going beyond standard moderator-by-treatment interaction by leveraging machine learning (ML) to evaluate treatment effect heterogeneity with greater accuracy and flexibility than standard ordinary least squares (OLS) regression [132, 136, 137]. Such benefits are integral to making progress on targeted treatments that can be matched to participants’ profiles based on neurocognitive, psychosocial, and sociodemographic attributes.

#### Qualitative analyses

Qualitative data will be gathered and analyzed to offer insights into individuals’ experiences with the Digital PAI. Open-ended responses to the HAT questionnaire, which encompass introspections and reflections on both advantageous and disadvantageous encounters and their impacts, will be subjected to qualitative analysis based on established frameworks [138, 139]. Initially, distinct text units will be detected and analyzed separately from their context to facilitate unbiased coding. These elements, called “meaning units,” will be reorganized methodically and thematically as “advantageous” or “disadvantageous” encounters and subjective viewpoints regarding their impacts. Finally, these themes will be categorized into higher-order classes, which will be named and described through logic and team consensus. This method will also be applied to the qualitative responses from the CRQ.

## Discussion

This RCT aims to assess the between-group efficacy, change mechanisms, and participant-level moderators of a low-intensity, guidance-on-demand, scalable Digital PAI designed to reduce anxiety and depression symptoms in community adults and university students. The Digital PAI will incorporate weekly 30-minute computer-administered online sessions with thrice-daily smartphone-delivered EMIs across 6 weeks. The placebo control group, a Self-Monitoring Placebo group, receives mood-monitoring EMAs administered during the same 6-week treatment period. Randomly selected participants will receive and use passive sensor wearables. Other functional and process outcomes, such as ER, PA, and QOL, will also be measured. By employing mediation approaches and precision medicine methods, this RCT aims to investigate outcomes beyond the main effects and identify who benefits most from the treatment. It heeds calls for accessible, data- and theory-driven mental healthcare strategies that are tailored to the diverse and dynamic needs of adults, particularly among emerging adults with a high prevalence of mental disorders and limited access to mental healthcare resources [140]. Together, findings can inform patient-centered care and catalyze the development of future-generation DMHIs.

Additionally, this RCT fills several critical gaps in the DMHI literature. First, it assesses a locally tailored Digital PAI, which was designed to target issues with the positive valence system, an understudied area in most CBT research. Prior CBT work has focused on decreasing NA and symptoms while neglecting to examine strategies that can boost PA and QOL outcomes [141, 142]. Building on prior research, this protocol includes both weekly 30-minute online sessions and frequent and regular EMIs over 6 weeks to enhance the application and generalization of therapy skills in daily routines. This integrated approach may generate scalable and sustained enhancements in attention control [143], ER [144], and reward processing [145, 146]. Importantly, this RCT includes 3-, 6-, and 12-month follow-ups, addressing the paucity of long-term data on DMHIs and contributing to the mounting need for evidence of long-term treatment outcomes [24]. Precision medicine methods (e.g., T-learner, GATES) will be applied to data from all participants, thereby offering valuable insights for stepped-care approaches [147] and treatment-matching strategies [148]. Since this RCT is pragmatic in nature, it is potentially highly relevant for improving the mental healthcare infrastructure for anxious and depressed community adults and university students in Singapore, a high-density, resource-constrained, and multicultural setting. Such efforts should be directed at culturally diverse as well as low- and middle-income countries (LMICs), where accessible and scalable DMHIs are still limited [24]. As accessibility to DMHIs is more limited in LMICs compared to high-income countries, this work is integral to establishing the efficacy and mechanisms of Digital PAI first in a diverse setting, such as Singapore, which could inform dissemination in LMIC settings. To this end, the results of this RCT can optimally inform data- and theory-driven patient-centered care and the delivery of future-generation DMHIs across various contexts.

Simultaneously, this RCT includes diverse methodological aspects to enhance ecological validity (generalizability) and internal validity. First, the utilization of piecewise MLM provides a fine-grained assessment of change outcomes [149], facilitating the separation of proximal and distal outcomes. Second, leveraging causal mediation analysis and SEM enables inquiries into whether enhancements in the positive valence system constructs (e.g., anhedonia, attentional control, reward sensitivity) function as plausible explanatory treatment mechanisms [150, 151], thereby identifying treatment targets consistent with the Research Domain Criteria (RDoC) framework [152]. Third, meta-learning algorithms (e.g., T-learner) will be implemented to develop prescriptive prediction models [137] that inform which subgroup benefits most from Digital PAI compared to the Self-Monitoring Placebo. Such efforts improve accuracy and clinical interpretability when examining treatment effect heterogeneity, moving beyond answering questions about between-group treatment efficacy. Finally, for randomly selected individuals, data extracted from passive sensor wearables can aid in identifying context- and time-specific variables that function as engagement metadata and moderators, potentially informing just-in-time adaptive interventions [153].

This RCT has some foreseeable limitations. First, despite the plan to use stringent statistical approaches, its dependence on self-reports may be subject to recall biases or social desirability. To reduce such biases, wearable data, including geolocation and sleep actigraphy indices, will be leveraged to complement and validate self-report markers. Second, dropout is an anticipated issue, particularly given the 12-month follow-up timeframe. Nonetheless, this RCT employs retention strategies, including automated and scheduled reminders, as well as pro-rated or tiered reimbursement, to maximize or incentivize engagement and minimize attrition. Third, although this RCT includes both community and university student participants, regardless of their intent to seek mental health treatment, its generalizability to high-severity clinical populations may be limited. Nevertheless, the pragmatic and inclusive recruitment strategy allows for a broad spectrum of symptom severity, enabling exploratory analyses to identify subgroups that may benefit most from the intervention. These efforts may thus inform future iterations of Digital PAI delivery across various settings.

Despite the limitations, this RCT has some strengths that reflect its clinical translational scientific value. First, this RCT uses a rare approach to integrating weekly 30-minute online sessions with thrice-daily EMI prompts to promote skill consolidation and generalization in diverse routine settings. Second, it also grounds itself in the positive valence systems domain of the RDoC paradigm [154], with the Digital PAI building on standard digital CBT frameworks. Third, this prospective study employs a pragmatic RCT design across multiple time points (baseline, mid-treatment, post-treatment, 3-month, 6-month, and 12-month follow-ups), allowing for the assessment of both proximal and distal efficacy. It leverages EMA, performance-based neurocognitive and social cognition tests, self-reports, and wearable data, improving measurement precision and richness. The mediation analysis methods (causal mediation and SEM) and moderation approaches (precision medicine) offer rigorous tests of theory-driven mechanisms of change and treatment effect heterogeneity. These efforts align with the National Institute of Health (NIH) Science of Behavior Change (SOBC) calls [155, 156]. Finally, the local tailoring of the Digital PAI for a multicultural Southeast Asian country contributes to global initiatives aimed at testing its translational impact, which can inform both stepped-care and stratified mental healthcare delivery.

Several clinical and policy implications merit attention if this RCT provides evidence of sustained between-group and within-group effectiveness of the Digital PAI. First, the Digital PAI may be feasibly integrated into mental healthcare services delivered in hospitals, social service agencies, and university settings to aid individuals struggling with mild to moderate levels of anxiety or depression. Such dissemination efforts should ideally target populations underserved by face-to-face psychotherapy, including those who experience mobility and transportation challenges. Given its concision, mobile format, and modular approach, the Digital PAI may be well-suited for integration into either stepped-care or stratified care delivery systems. With further testing, the use of real-time digital phenotyping, EMA, and EMI in conjunction with moderator outcomes may inform the development of automated triaging systems facilitated by artificial intelligence. If validated, the Digital PAI protocol can be applied in other culturally diverse contexts beyond Singapore, informing mental health policies that promote the implementation of a cost-effective and scalable strategy. Moreover, the modular approach facilitates adaptation for various clinical applications and populations, such as behavioral medicine, as well as physical and psychiatric comorbidities. High-demand and low-resource settings that can benefit from DMHIs, such as the Digital PAI, are manifold, including but not limited to community youth settings, secondary schools, the military, and workplace organizations. To summarize, this RCT lays the groundwork for a high-impact, precision-guided model of mental healthcare delivery that integrates patient-centered care, prevention science, and population-level accessibility.

